### Study design

An information brochure on the study will be given to all patients who meet the inclusion criteria of the study at the preoperative consultation. An evaluation of pain by EVA scale will be carried out during this consultation.

After obtaining the patient’s consent on the day of the operation, the allocation between the two groups will be done by randomisation. This randomisation will be stratified on the centre and uterine volume (280-500g; > 500g). The randomisation list will be a randomised computer list established before the beginning of the study. It will be balanced by blocks of variable size and centralised via the Ennov Clinical web platform.

Two groups of patients will be constituted: a “laparoscopic approach” group and a “vNOTES” group. Patients will not know their group of assignment.

All hysterectomies will be performed by vNOTES-trained surgeons (20 procedures performed) who will follow the standard operating procedure. In women assigned to the experimental arm, the surgeon will perform a hysterectomy with the vNOTES medical device. In the women assigned to the control arm, the surgeon will perform a laparoscopic hysterectomy.

A questionnaire assessing visual comfort, feeling of safety and satisfaction on Lickert scales will be completed immediately after surgery by the operator and the operating assistant.

The care provided by the anesthetists and nurses will be standardised and similar in both groups. To limit bias, in all cases the patient will have abdominal dressings as if it underwent a laparoscopy.

Once returned to the ward, all participants will be assessed every 2 hours and discharged home when the patient’s condition allows(Chung score ≥ 9/10).

Telephone interviews by the department CRA, blinded to the allocation group will be conducted daily for the first week to assess postoperative pain.

A follow-up visit by an independent adjudication committee, blinded to the allocated group will be performed 6 weeks postoperatively or earlier if a complication brings a patient to consult.

Finally, a telephone call will be made at 3 months to evaluate the sexual impact by a questionnaire (PISQ12 with a score ranging from 0 to 48) (Table I).

**Table I t001:** Conduct of the study.

Visits	V1	V2	V3	V4	V5	V6
Title of the visit	Pre-operative selection visit	Day of the intervention	Immediate post-operative follow-up	Telephone follow-up D1-D7	Post-operative visit at 6 weeks	Questionnaire at 3 months
Information	X					
Eligibility Criteria	X					
History of comorbidities	X					
Consent		X				
Randomisation		X				
Intervention*		X				
Adverse events		X	X	X	X	
Chung's score **			X			
Post-operative pain assessment ***			X	X		
Clinical examination ****					X	
Sexuality Questionnaire						X

X specific acts to research; *According to the allocated group; **Chung score; ***by scale from 0 (no pain) to 10 (maximum pain); ****standardised clinical examination: general condition, BP, abdominal palpation, vaginal examination.

The study protocol has been validated (N° clinical trial : NCT05884658).

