**Materials and Methods:**

A randomised, double-blind, superiority trial will be performed at five hospital centres. Women with benign uterine pathology requiring hysterectomy and with a large uterus (> 280g) will be randomised to receive either laparoscopic or vNOTES hysterectomy.

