## Material and Methods

### Type of study

This is a prospective, open-label, multicentre, randomised, parallel-group superiority study stratified on centre and uterine volume (280-500g; >500g). It evaluates conversion and intraoperative and postoperative complications within 6 weeks of surgery using the transluminal natural orifice vaginal endoscopic system for hysterectomies (vNOTES) versus laparoscopic hysterectomy.

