### Outcomes

The primary outcome is a composite endpoint including the occurrence of intraoperative and postoperative complications within 6 weeks of surgery. Intraoperative complications will be defined as injury to surrounding organs (bladder, ureters, rectum, colon, small intestine) or bleeding requiring immediate resumption, intraoperative transfusion and/or decreasing the patient’s haemoglobin by more than 2 points compared to the last known pre-operative blood test. Postoperative complications will be defined according to the Clavien-Dindo classification.

Regarding secondary outcomes, the need for conversion during surgery will be collected.

Post-operative pain at day 0 will be evaluated by the maximum daily pain felt on arrival in ambulatory surgery and at hour 3 after return from the block. Short-term postoperative pain during the first week after surgery will be measured by a numerical scale (0 to 10), determined on a daily telephone call. The consumption of analgesics other than those planned in the study in the immediate postoperative period and within 7 days will also be recorded. The duration of postoperative reflex ileus will be measured between the day of the operation and the resumption of a transit (appearance of the first gas) in hours. The duration of the operation from the incision to the end of the closure (in minutes). The duration of hospitalisation will be evaluated in days and the possibility of returning home by the time in hours between the surgical incision and the achievement of a Chung≥ score of 9/10. Sexual disorders: sexual life will be assessed by the difference in the specific validated score (self-questionnaire) (PISQ12 with a score ranging from 0 to 48) between the inclusion date and 3 months after surgery for sexually active women. The visual comfort, satisfaction and feeling of safety of the surgeon and the operating assistant will be evaluated via a Likert scale.

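### The open-ended patient-masking claim rests on abdominal dressings alone: it cannot hold for PISQ-12 at 3 months and is not assured for self-rated pain to day 7

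*Protocol article*

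**What the plan says.** The abstract and the methods label the design differently. The abstract (Materials and Methods) states: "A randomised, double-blind, superiority trial will be performed at five hospital centres". The section Type of study states: "This is a prospective, open-label, multicentre, randomised, parallel-group superiority study stratified on centre and uterine volume".

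Study design then makes a general statement about the patient: "Patients will not know their group of assignment". No end date is attached. Later in that section comes the one step that serves this purpose, introduced as a way to limit bias: "in all cases the patient will have abdominal dressings as if it underwent a laparoscopy". The article describes no sham skin incision and does not say how long the dressings stay on.

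Three patient-reported outcomes follow surgery:

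- **Pain, days 1 to 7.** Women are "discharged home when the patient’s condition allows", judged by the Chung score. After that: "Telephone interviews by the department CRA, blinded to the allocation group will be conducted daily for the first week to assess postoperative pain". Outcomes adds: "Short-term postoperative pain during the first week after surgery will be measured by a numerical scale (0 to 10), determined on a daily telephone call".
- **Analgesics beyond those planned**, recorded in the immediate postoperative period and within 7 days.
- **PISQ-12**, a self-questionnaire scored 0 to 48, taken by telephone at 3 months and analysed as change from inclusion in sexually active women.

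Statistical analysis treats the secondary objectives as exploratory. Effect estimates with 95% confidence intervals are given, without p-values.

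**The concern.** For pain, analgesic need and sexual function, the patient is the assessor. Masking the person who telephones does not protect a rating given by a woman who knows her own arm, and she may also tell the caller.

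The dressing imitates wounds that a vNOTES patient is not expected to have. Once it is off, intact skin identifies vNOTES. Port wounds point to laparoscopy, or to a converted vNOTES procedure. The masking therefore has a natural end, while the article's claim has none.

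The Discussion lists less postoperative pain among the benefits sought for patients. A woman who learns that she had the newer technique without abdominal scars may rate her recovery more favourably, which would tilt these comparisons towards vNOTES. A reader told that patients did not know their group would have no reason to allow for this.

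**Working it through.** The article gives no figure to reproduce on this point. The check sets the timing of the masking against the timing of each patient-reported outcome.

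**Inputs**

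- Masking measure: abdominal dressings in both arms, period of wear not stated (Study design).
- Pain calls: daily, D1 to D7, so 7 ratings per patient (Table I; Study design).
- PISQ-12: 3 months (Table I; Study design; Outcomes).
- Conversion during surgery: possible, and listed as a secondary outcome (Outcomes).

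**PISQ-12 at 3 months.** No postoperative dressing is in place at 3 months. With no sham incision described, a woman with unconverted vNOTES has no port scars to see. A converted vNOTES patient may have abdominal wounds and so may not be able to tell. The masking therefore fails at least for unconverted vNOTES patients, whatever the dressing period was.

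**Pain and off-plan analgesics to day 7.** Let d be the day of dressing removal, with removal after that day's call. The ratings given after removal number 7 − d for d from 0 to 7, and none if removal is later. The value of d is an assumption, because the article does not give it:

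| Removal day d (assumed) | Ratings after removal, of 7 |
|---|---|
| before the first call (d = 0) | 7 − 0 = 7 |
| day 2 | 7 − 2 = 5 |
| day 4 | 7 − 4 = 3 |
| day 7 or later | 0 |

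The article supports only the full range of 0 to 7. Pain on day 0, taken on arrival in ambulatory surgery and at hour 3, falls when the dressings are most likely in place and is not in question.

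**Labels.** Double-blind in the abstract and open-label in the methods cannot both describe the trial. The details in Study design fit neither label well: the patient, the telephone interviewer and the 6-week committee are said not to know the group, while the operator necessarily does.

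**The case against.** The strongest reply is that the length of dressing wear and the instructions to patients are operational details that an article leaves to the full protocol, so silence on them proves nothing. This stands for pain to day 7. A reader might infer that patient blinding fails for first-week pain, but the article does not say when dressings come off, and they could stay on all week. Masking there is unassured, not shown to be absent.

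The reply does not rescue the 3-month outcome, since no plausible dressing period reaches it. What is criticised there is a positive statement without an end date.

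A second reply is that the methods call the trial open-label and offer the dressings only as a way to limit bias, so nothing false need be reported. That has some force, but the same article says double-blind in its abstract and states flatly that patients will not know their group.

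Third, these outcomes are exploratory and carry no tests, and partial masking is common in surgical trials. That is fair, and it limits the weight of the point.

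Two other stronger readings should be resisted. One is that every PISQ-12 answer in both arms is unmasked: conversions make that too absolute, and intact skin after vNOTES is itself inferred from the vaginal route and from dressings applied in imitation of laparoscopy. The other is that this point undermines the primary outcome. It concerns the patient as assessor; complications are assessed by a committee that the article describes as blinded, and whether that committee can stay so is a separate question, not argued here.

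**Conclusion.** The point holds in a limited form. The open-ended claim that patients will not know their group is wrong for PISQ-12 at 3 months, at least among women with unconverted vNOTES. For self-rated pain and off-plan analgesic use to day 7 it is not assured, with 0 to 7 of the 7 daily ratings potentially given after unmasking. The double-blind and open-label labels contradict each other.

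This rests on two assumptions: that no sham skin incision is made (none is described), and that unconverted vNOTES leaves no abdominal port wounds. If the full protocol specified sham incisions, the PISQ-12 conclusion would need to be revisited.

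The size and direction of any resulting shift cannot be derived from the article; a tilt towards vNOTES is plausible but is a judgement. The sample size is not affected. The correction is worth making because the present wording claims a property that the described design does not have, and restating it costs little.

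**What to change.** 1. Reconcile the double-blind and open-label labels, and state who is masked, for which outcomes and until when.
2. Replace the open-ended statement with: *patients are masked only while the abdominal dressings are in place*.
3. Report PISQ-12 as an unmasked patient-reported outcome.
4. Reconcile the dressing period with the day 1 to 7 call period, as site wound care allows. Otherwise report pain and off-plan analgesic use over those days as possibly unmasked.
5. Ask patients not to describe their abdomen to the blinded caller.
6. Keep the pain comparison on all randomised patients at fixed days. Do not split it at each woman's dressing removal: removal happens after randomisation and its timing may differ by arm, so the split would lose the protection of randomisation.
7. Optionally, add one question on guessed allocation at the day-7 call, asked after the pain rating. Use it descriptively only, because a guess may reflect how much pain the woman had as well as what she saw.

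The cost is protocol wording, one instruction to patients and at most one question in a call already planned. The downside is a weaker masking claim for PISQ-12 and possibly for later pain ratings.

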## Introduction

In France, there are 62,000 hysterectomies performed per year, of which 70% are for benign indications (Lee et al., 2019).

The choice of surgical approach (laparotomy, laparoscopy or vaginal route) is particularly important in cases with large uteri (> 280g) as these are recognised to be associated with a high risk of complications and conversion. Currently minimally invasive approaches are recommended by the Collège national des gynécologues et obstétriciens français (CNGOF) (grade C) (Deffieux et al., 2015).

The vaginal and the laparoscopic route have their advantages and disadvantages.The latter is associated with an increased rate of conversion to laparotomy and post operative complications compared with vaginal hysterectomy (15% for the vaginal route, 37.5% for laparoscopy) and is particularly true for large uteri > 280g (Lee et al., 2019; Daraï et al., 2001; Gendy et al., 2011).

A Medical Device, the vNOTES (Natural Vaginal Orifice Transluminal Endoscopy System), offers the advantage of minimally invasive surgery by endoscopy through the vagina. Several feasibility studies in gynaecological surgeries have already been performed (Baekelandt, 2018a; Baekelandt, 2018b; Baekelandt et al., 2018c; Lowenstein et al., 2020; Baekelandt, 2019). Randomised trials have shown that the vNOTES allows hysterectomies to be performed without conversion with less pain, fewer postoperative complications and a shorter hospital stay when compared to laparoscopy (Baekelandt et al., 2019; Baekelandt et al., 2021). More recently, the developers of vNOTES found favorable results for vNOTES in terms of conversion and complication rates (Nulens et al., 2021) in large volume uteri (>280g).

The main objective of our study is to demonstrate the superiority in terms of intra and post operative complications within 6 weeks after surgery with the use of a vNOTES hysterectomy versus laparoscopic hysterectomy for benign pathologies on estimated large volume uteri (>280g).

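### The committee described as blinded examines the abdomen itself at 6 weeks, so its blinding probably cannot be kept for most women, which mainly affects the postoperative part of the primary outcome

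*Protocol article*

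**What the plan says.** - **Who makes the visit.** Study design: "A follow-up visit by an independent adjudication committee, blinded to the allocated group will be performed 6 weeks postoperatively". The same sentence allows an earlier visit when a complication leads the patient to consult.
- **What the visit contains.** The Table I footnote describes it as "standardised clinical examination: general condition, BP, abdominal palpation, vaginal examination".
- **Concealment.** Study design: "in all cases the patient will have abdominal dressings as if it underwent a laparoscopy". The article describes no sham skin incision, no covering of the abdomen at 6 weeks and no classification from redacted files.
- **Access routes.** The Introduction says that vNOTES "offers the advantage of minimally invasive surgery by endoscopy through the vagina". For the control arm, Study design says: "In the women assigned to the control arm, the surgeon will perform a laparoscopic hysterectomy".
- **Primary outcome.** Outcomes: "The primary outcome is a composite endpoint including the occurrence of intraoperative and postoperative complications within 6 weeks of surgery". For the postoperative part: "Postoperative complications will be defined according to the Clavien-Dindo classification". No minimum grade is given.
- **Labels.** The Abstract calls the trial double-blind; Type of study calls it open-label.

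**The concern.** The surgeon cannot be blinded, so blinded assessment is the main protection for the primary outcome. The article claims that protection for the committee and also gives the committee the task most likely to remove it, an in-person examination of the abdomen. The earlier, complication-driven visits are the more sensitive ones: any wounds are fresher, and these women are the most likely to count as events.

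The analysis compares the proportions of women with at least one complication. Whether a minor postoperative deviation counts can therefore decide a woman's result, and that is a judgement. If it is made with the arm known, in a trial that sets out to show vNOTES superior, the calls could drift towards the expected answer while the report describes the assessment as blinded.

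**Working it through.** The article gives no figure for this point, so the first check is to set its statements side by side.

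1. The committee sees the patient and is called blinded (Study design).
2. The visit includes abdominal palpation (Table I footnote).
3. Laparoscopy enters through the abdominal wall; vNOTES enters through the vagina (Introduction, Study design).
4. The dressings imitate a laparoscopy after surgery (Study design). The article does not say when they come off. That they are gone by 6 weeks, and that port scars can then be seen, is an inference.
5. From 1 to 4, someone palpating the abdomen will usually see whether there are port sites. A vNOTES case converted to an abdominal route would also have abdominal wounds, so the sign is strong but not perfect.
6. The primary outcome window closes at the same 6 weeks (Outcomes).

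The vaginal examination is not counted as unmasking. Data collection records the solidity of the vaginal suture without distinguishing the arms, so nothing in the article suggests that it reveals allocation.

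**Which part of the outcome is exposed.** The intraoperative part reads "Intraoperative complications will be defined as injury to surrounding organs (bladder, ureters, rectum, colon, small intestine) or bleeding requiring immediate resumption", and goes on to transfusion or a haemoglobin fall of more than 2 points. These are mostly facts fixed around surgery, and a scar seen at 6 weeks can hardly alter them. The Clavien-Dindo part is where judgement enters.

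**Illustration of size (the bias is assumed).** Inputs: n = 119 per arm and two-sided 5% (5% and 119 are from Sample size calculation; two-sided is assumed). The true rate p is the same in both arms: 15% and 37% are the planning rates, and 26% is their midpoint, (15 + 37)/2. A relative share r of vNOTES events is not counted, so the observed vNOTES rate is q = p(1 − r) and the spurious relative risk is 1 − r.

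With p̄ = (p + q)/2, SE₀ = √[2p̄(1 − p̄)/n] and SE₁ = √{[p(1 − p) + q(1 − q)]/n}, the normal approximation gives

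P(significant) = Φ{[(p − q) − 1.96·SE₀]/SE₁} + Φ{[−(p − q) − 1.96·SE₀]/SE₁}.

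Example, p = 0.26 and r = 0.20:
- q = 0.208 and p̄ = 0.234
- SE₀ = √(0.35849/119) = 0.0549
- SE₁ = √(0.35714/119) = 0.0548
- first term Φ[(0.052 − 0.1076)/0.0548] = Φ(−1.01) ≈ 0.155
- second term ≈ 0.002
- total 0.157

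| True rate, both arms | r = 0 | r = 10% | r = 20% |
|---|---|---|---|
| 15% | 0.050 | 0.063 | 0.104 |
| 26% | 0.050 | 0.075 | 0.157 |
| 37% | 0.050 | 0.092 | 0.227 |

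In women, the uncounted events run from 119 × 0.15 × 0.10 ≈ 1.8 to 119 × 0.37 × 0.20 ≈ 8.8, so about 2 to 9 calls in one arm. The planned Fisher's exact test is more conservative than this approximation, so its probabilities would be somewhat lower.

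**The case against.** The strongest reply is that the article describes a visit, not an adjudication procedure. It does not say how, when or from what sources the committee classifies events, and an article may leave that to the full protocol. Table I also records adverse events on the day of surgery, in the immediate postoperative period and during the day 1 to 7 calls, so many events are on record before the 6-week visit. The intraoperative items are mostly objective, and converted vNOTES cases blur the sign.

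All of this stands, and it limits the point. A reader might infer that the primary outcome as a whole is not adjudicated blind. The documents do not support that: they never say that the committee classifies the whole composite from this visit, and they do not describe what the committee reads about the operation. That it classifies events at all around this time is implied by its name and by the 6-week window, not stated.

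The reply does not rescue the blinding claim for the visit. Who examines, what is examined and that the examiner is blinded are all stated, and they do not fit together. That is a conflict between stated elements, not a missing detail.

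**Conclusion.** The point holds in a limited form. As described, the committee's blinding probably cannot be maintained at the 6-week or earlier visit for most women. The consequence falls mainly on the postoperative Clavien-Dindo component. This rests on two inferences, that dressings are off and that port sites are visible at the visit; both follow closely from the two access routes.

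The size of any bias is unknown. If 10% of vNOTES events went uncounted because the arm was known, the chance of a significant result with no true difference would be about 6-9% instead of 5%. With 20% it would be about 10-23%. Because part of the composite is objective, a 20% loss across all events would need a larger distortion within the judged part. The figures show what is at stake and do not predict it.

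**What to change.** Separate examining from classifying, without adding a visit.

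- Keep an independent examiner for the 6-week or earlier visit. That person records findings on a standard form and does not classify that patient's events.
- Have existing committee members who have not seen the patient classify all her events, those recorded from the day of surgery onwards and those found at the visit. They work from a coded file with allocation, approach and any description of incisions or ports removed.
- If this is not done, state plainly that the 6-week assessment is not blind.
- In either case, reconcile double-blind in the Abstract with open-label in Type of study by saying who is blinded and to what.

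Keeping the examiner independent matters. Passing the visit to the site's usual clinician could move the bias from classification to detection, and redacted files cannot recover events that were never recorded.

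The cost is redaction work for the existing research team. Two weaknesses remain: some event descriptions may still reveal the approach, and the recording of findings at the visit itself stays unmasked.
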